## Abstract

**Background:**

The first-line treatment for common bile duct stones (CBDS) is endoscopic transpapillary stone removal, typically performed using either endoscopic sphincterotomy (EST) or endoscopic papillary balloon dilation (EPBD). However, EST is associated with risks of bleeding and perforation, while EPBD carries a significant risk of post-procedural pancreatitis. Recently, a combined approach involving minimal EST followed by EPBD (ESBD) has been reported to mitigate these drawbacks, offering potentially safer and more effective outcomes. Nevertheless, no prospective study has adequately evaluated the utility of ESBD, as prior studies were mainly observational or limited by small sample sizes. Therefore, we designed a randomized controlled trial to investigate whether ESBD is superior to EST for the treatment of small CBDS.

**Methods:**

This study is a multicenter, randomized, open-label, parallel-group trial; outcome assessors will not be blinded, but objective predefined criteria will be used to minimize bias. Eligible participants will include patients aged 18 years or older diagnosed with CBDS who require endoscopic stone removal, with eligibility confirmed via imaging modalities. After confirming eligibility, patients will be randomly assigned in a 1:1 ratio to either the ESBD group or the EST group. In the ESBD group, a minimal sphincterotomy will first be performed, followed by balloon dilation for stone extraction. In the EST group, a medium incision extending beyond the hooding fold will be performed prior to stone extraction. The primary endpoint is the incidence of procedure-related adverse events, including pancreatitis, bleeding, and perforation. Secondary endpoints include technical success rate, clinical success rate, procedure time, need for lithotripsy, and stone recurrence rate.

**Discussion:**

This study is the first multicenter, randomized controlled trial to prospectively evaluate the efficacy and safety of ESBD for the treatment of small CBDS. The findings are expected to determine whether ESBD can serve as a new standard therapeutic option compared with conventional EST.

**Trial registration:**

Japan Registry of Clinical Trials: jRCT1040250008. Registered on 21 April 2025. (https://jrct.mhlw.go.jp/en-latest-detail/jRCT1040250008).

## Administrative information

Note: The numbers in curly brackets in this protocol refer to SPIRIT checklist item numbers. The order of the items has been modified to group similar items (see http://www.equator-network.org/reporting-guidelines/spirit-2013-statement-defining-standard-protocol-items-for-clinical-trials/).

## Introduction

### Background and rationale {6a}

Endoscopic retrograde cholangiopancreatography (ERCP) is the first-line treatment for common bile duct stones (CBDS) [1]. Stone removal is typically performed transpapillarily using a retrieval basket and balloon catheter. Papillary intervention is required to extract stones into the duodenum, as the sphincter of Oddi functions as a mechanical barrier. For small stones (generally ≤ 10 mm), the standard approaches are endoscopic sphincterotomy (EST) or endoscopic papillary balloon dilation (EPBD) [2].

EST involves incising the sphincter to create a wider opening, thereby facilitating stone removal. However, this technique carries risks such as bleeding and perforation. In contrast, EPBD is technically easier to perform and is associated with a lower risk of bleeding and perforation. However, it may impact the pancreatic duct orifice and is associated with a higher risk of post-ERCP pancreatitis. Given the trade-offs of each technique, the choice between EST and EPBD is often based on patient background and endoscopist preference, though EST remains the more commonly used approach.

Recently, a combination technique involving minimal EST followed by EPBD (ESBD)—has been proposed as a way to offset the limitations of EST and EPBD. While conventional EST involves a medium incision that extends beyond the hooding fold, ESBD employs a smaller incision limited to above the fold, potentially reducing the risk of bleeding and perforation, while the subsequent balloon dilation may still ensure adequate orifice opening. Furthermore, ESBD is hypothesized to reduce the risk of pancreatitis compared with EPBD alone by directing the dilation force away from the pancreatic duct and allowing controlled pressure release.

A retrospective study [3] reported in 2020 compared 114 cases of EST and 321 cases of ESBD, demonstrating that the ESBD group had significantly lower rates of requiring multiple sessions (35.1% vs. 12.8%, *P* < 0.001), shorter procedure time for stone removal (31.6 min vs. 25.8 min, *P* = 0.01), and reduced need for mechanical lithotripsy (16.7% vs. 7.8%, *P* = 0.01). The adverse event rate was also significantly lower in the ESBD group (15.8% vs. 4.4%, *P* < 0.001), particularly for bleeding (7.9% vs. 0.9%, *P* < 0.001), without a significant increase in pancreatitis (2.6% vs. 1.9%, *P* = 0.62).

More recently, in 2024, a randomized controlled trial [4] comparing EST and ESBD reported that the primary endpoint, use of mechanical lithotripsy, was significantly lower in the ESBD group (20.0% vs. 4.0%, *P* = 0.028), and procedure time was also significantly shorter (18.5 min vs. 17.0 min, *P* = 0.047). However, the trial was prematurely terminated due to poor enrollment and included only 100 participants (50 per group) instead of the planned 220, which limits the generalizability of its findings.

Given these promising but preliminary data, ESBD is expected to be a valuable technique for managing small CBDS; however, no prospective studies have yet adequately evaluated its safety and efficacy. Therefore, we designed this randomized controlled trial to determine whether ESBD provides superior outcomes compared with conventional EST and to assess its potential as a new standard approach for papillary treatment during endoscopic management of small CBDS. Previous studies have been limited by small sample sizes, single-center designs, and heterogeneous protocols. The present trial addresses these limitations through a larger sample size, multicenter participation, and standardized procedural protocols.

### Objectives {7}

The objective of this study is to compare the efficacy and safety of ESBD and EST in patients undergoing endoscopic transpapillary removal for small CBDSs. The primary aim is to determine whether the incidence of procedure-related adverse events is significantly lower in the ESBD group. Additionally, secondary comparisons will be made regarding outcomes related to stone removal efficacy, such as the proportion of cases requiring mechanical lithotripsy and the overall procedure time. Details of the study outcomes are summarized in Table 1.

**Table 1 Tab1:** The primary and secondary endpoints in the MARBLE trial

Outcome	Measurement variable/definition	Analysis metric	Time point

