**Secondary endpoints**			
Type and severity of procedure-related AEs	Classified using ASGE lexicon; detailed criteria applied for bleeding and pancreatitis (see Notes)	Descriptive	Within 30 days from the procedure
Technical success rate	Completion of ESBD or EST according to protocol	Binary outcome	Day of procedure
Clinical success rate	Complete stone removal in a single session	Binary outcome	Day of procedure
Total procedure time	Time from cannulation to completion of stone removal	Continuous (minutes)	Day of procedure
Time required for stone removal	Time from end of ESBD or EST to completion of stone removal	Continuous (minutes)	Day of procedure
Proportion of cases requiring lithotripsy	Use of mechanical lithotripsy (excluding mechanical tools used without fragmentation), electrohydraulic lithotripsy, or laser lithotripsy	Incidence proportion	Day of procedure
Stone recurrence rate	Reappearance of bile duct stones post-removal	Incidence proportion	5-year follow-up
Time to stone recurrence	Days from successful stone removal to confirmed recurrence	Time-to-event	5-year follow-up
Biliary event rate	Any biliary event (e.g., stone recurrence, cholangitis, cholecystitis, liver abscess, biliary cancer)	Incidence proportion	5-year follow-up
Time to biliary event	Days from successful stone removal to occurrence of any biliary event	Time-to-event	5-year follow-up
**Notes on adverse event definitions** The definitions and severity grading of procedure-related adverse events will follow the ASGE lexicon [7]. Among these, bleeding and pancreatitis are the most anticipated adverse events in this study and represent key safety outcomes; therefore, more detailed criteria are specifically defined for these two events **-Bleeding:** *Intra-procedural bleeding*: requires hemostatic intervention (excluding preventive measures) *Post-procedural bleeding*: confirmed by endoscopy or imaging study such as computed tomography, or inferred from clinical findings such as hematemesis, melena, or a drop in hemoglobin level that cannot be explained by other causes **-Pancreatitis:** The diagnosis is established when at least two of the following three criteria are met: (1) acute abdominal pain and tenderness in the upper abdomen, (2) elevated levels of serum or urinary pancreatic enzymes, and (3) imaging findings indicative of acute pancreatitis [8]			

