## Statistical methods

### Statistical methods for primary and secondary outcomes {20a}

For the primary outcome, group comparisons of categorical variables will be performed using Pearson’s chi-square test or Fisher’s exact test, as appropriate. A two-sided *p*-value of less than 0.05 will be considered statistically significant.

For secondary outcomes, categorical variables will also be analyzed using Pearson’s chi-square test or Fisher’s exact test. Continuous variables will be compared using the *t*-test or the Mann–Whitney *U* test, depending on the distribution. Normality of continuous variables will be assessed using the Shapiro–Wilk test before applying the *t*-test. Time-to-event variables will be analyzed using the log-rank test, and survival curves will be constructed using Kaplan–Meier estimates. To examine factors associated with each event, multivariable analyses such as linear regression, logistic regression, and Cox proportional hazards models will be applied with covariate adjustment. For multiple subgroup analyses, Bonferroni correction will be applied to adjust the p-value threshold to control the family-wise error rate. If the proportion of missing data exceeds 10%, multiple imputation will be conducted as a sensitivity analysis in addition to the available-case analysis. A two-sided *p*-value < 0.05 will be considered statistically significant for all analyses. All analyses will be performed using R.

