### Methods for additional analyses (e.g., subgroup analyses) {20b}

Subgroup analyses will be conducted based on the following variables: sex, age, body mass index, performance status, comorbidities, presence of liver cirrhosis or renal failure, history of acute pancreatitis, use of antithrombotic agents (none, antiplatelet agents, anticoagulants), platelet count, PT-INR, presence of cholangitis, gallbladder, or gallstones, common bile duct diameter, size and number of bile duct stones, endoscopist’s ERCP experience (< 200 or  ≥ 200 procedures), presence of periampullary diverticulum, use of rectal NSAIDs, pancreatic duct guidewire placement, and placement of a pancreatic stent.

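### The stone-removal comparisons are specified as unadjusted tests although stone size, stone number and duct diameter are trial variables; the tests are valid but give up precision, chiefly for the two procedure times

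*Protocol article*

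**What the plan says.** The Objectives section makes stone-removal efficacy the second aim of the trial: "secondary comparisons will be made regarding outcomes related to stone removal efficacy, such as the proportion of cases requiring mechanical lithotripsy". How long the procedure takes is its other example. Table 1 lists the endpoints concerned: lithotripsy, clinical success (complete removal in one session), total procedure time, and time required for stone removal, defined as "Time from end of ESBD or EST to completion of stone removal".

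Section 20a fixes how the arms are compared. For secondary outcomes, "categorical variables will also be analyzed using Pearson’s chi-square test or Fisher’s exact test", and "Continuous variables will be compared using the *t*-test or the Mann–Whitney *U* test, depending on the distribution". The regression models come with their own stated purpose: "To examine factors associated with each event, multivariable analyses such as linear regression, logistic regression, and Cox proportional hazards models will be applied". These models are to be adjusted, but no covariates are named, and the models are not tied to the ESBD versus EST effect.

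Section 20b lists, as subgroup variables, "gallbladder, or gallstones, common bile duct diameter, size and number of bile duct stones". Stone diameter also has to be judged before enrolment, because Table 2 excludes stones of 12 mm or more. Section 16a stratifies randomisation on pre-procedural biliary drainage and antithrombotic use only.

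**The concern.** Stone burden plausibly drives how long extraction takes, whether a stone must be crushed, and whether the duct is cleared in one session. The documents do not quantify this, so it is an assumption, though a reasonable one. The trial holds these variables and does not balance them by design, yet the stated comparisons ignore them. Variation that a baseline covariate could explain stays in the error term, so intervals are wider and power is lower than they need be.

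This is more than detail left to an analysis plan. The article names the between-arm tests, and it separately says what the adjusted models are for. What is at stake is the precision of the secondary efficacy answer.

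**Working it through.** **The plan's own figure.** Section 14 gives 280 patients (140 per arm) for the primary endpoint, from 15.8% vs 4.4%, two-sided α = 0.05, 80% power and 10% loss. The continuity-corrected chi-square formula gives 126 per arm, and 126/0.90 = 140. The target reproduces. It does not depend on the present point. No SD, R² or power is stated for the stone-removal endpoints.

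**Procedure times, general.** A linear model whose baseline covariates explain a share R² of the variance multiplies the standard error by √(1 − R²). The equivalent number per arm is 140/(1 − R²).

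| Assumed R² | SE ratio | Equivalent n per arm |
|---|---|---|
| 0.1 | 0.95 | 156 |
| 0.2 | 0.89 | 175 |
| 0.3 | 0.84 | 200 |
| 0.4 | 0.77 | 233 |

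**Procedure times, retrospective study (Background).** Inputs are 31.6 vs 25.8 min, 114 EST and 321 ESBD cases, P = 0.01. Assume that these are means compared by t-test (normal approximation):
- z = 2.576, so SE = 5.8/2.576 = 2.25 min.
- √(1/114 + 1/321) = 0.1090, so SD = 2.25/0.1090 ≈ 20.7 min. If P was rounded from between 0.005 and 0.015, the SD lies between about 19 and 22 min.
- With 140 per arm, power = Φ(5.8/(SD·√((1 − R²)·2/140)) − 1.96).
- At R² = 0: 5.8/(20.7 × 0.1195) = 2.34, and Φ(0.38) ≈ 65%.
- At R² = 0.1/0.2/0.3/0.4: about 70/75/80/86%.

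**Procedure times, 2024 randomised trial (Background).** Inputs are 18.5 vs 17.0 min, 50 per arm, P = 0.047. On the log scale:
- ln(18.5/17.0) = 0.0846 and z = 1.986, so SE = 0.0426.
- Log-SD = 0.0426/√(2/50) ≈ 0.21.
- With 140 per arm and no adjustment: 0.0846/(0.213 × 0.1195) = 3.32, and Φ(1.36) ≈ 91%.
- At R² = 0.1 to 0.4, the same formula gives about 94% to 99%.

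This back-calculation is inexact if the figures are medians or the test was rank-based. On the same log scale the retrospective figures imply ln(31.6/25.8)/(2.576 × 0.1090) = 0.2028/0.2808 ≈ 0.72. The two sources therefore span a wide range, and the gain depends on which is nearer the truth.

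**Lithotripsy.** At 16.7% vs 7.8% with 140 per arm, unadjusted power is 62% by formula. A simulation of 2,000 trials per case compared Pearson's test with logistic regression on arm and one standardised covariate:

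| Assumed log-odds per SD | Unadjusted power | Adjusted power | SE ratio, standardised risk difference |
|---|---|---|---|
| 0.5 | 65% | 64% | 0.99 |
| 1.0 | 63% | 66% | 0.94 |
| 1.5 | 65% | 72% | 0.90 |

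The change is about −1 to +7 points, and the −1 is within simulation error. With 10% in both arms (log-odds 1.0 per SD), both tests rejected in 4.4% of trials, so neither is invalid. Expected events are 140 × (0.167 + 0.078) ≈ 34, which limits how many covariates the model can carry.

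**Clinical success.** The nearest documented rates are those for needing multiple sessions, 35.1% vs 12.8%. Unadjusted power at 140 per arm is already about 99%.

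**The case against.** The strongest reply is that nothing here is wrong. Unadjusted tests in a randomised trial keep their type I error, and section 20a already plans linear, logistic and Cox models with covariate adjustment. Linear regression can apply only to continuous outcomes, and the continuous endpoints in Table 1 are the two times. Adjusted models for the times are therefore foreseen, and whether arm is a term could be settled in the analysis plan that section 21b mentions.

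The validity argument stands in full. The second argument stands in part: the text does not say that arm is excluded from these models. It does give the between-arm comparison to the unadjusted tests and the models to another purpose, so the adjusted estimate has no declared role.

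A reader might go further and infer that a chance imbalance in stone burden would be misreported as a technique effect. The documents do not support that. With 140 per arm, the standardised difference of an unstratified covariate has SD √(2/140) = 0.12, and it exceeds 0.2 in about 9% of trials. That is random error, already covered by the test level and the interval width, and not bias. A reader might also infer that the loss decides the efficacy answer. At the variability implied by the 2024 trial, it would not.

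Two further cautions stand. Excluding stones of 12 mm or more narrows the range of stone size and may weaken its prognostic value. The article also does not say when stone number and duct diameter are measured.

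**Conclusion.** The point holds as one of efficiency. The stated treatment comparisons for the stone-removal endpoints are unadjusted, and the adjusted models serve another purpose. Making a prespecified adjusted model the comparison would be a better use of data that the trial lists.

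The benefit lies mainly in the two procedure times: roughly 5 to 21 points of power if the retrospective figures are means from a t-test and R² is 0.1 to 0.4, and much less if variability is as low as the 2024 trial's P value implies. R² is an assumption throughout. The gain is small for lithotripsy and negligible for clinical success at the documented rates.

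The 5-year analysis invites a similar reading. The biliary endpoint is "Any biliary event (e.g., stone recurrence, cholangitis, cholecystitis, liver abscess, biliary cancer"), cholecystitis needs a gallbladder, and "Time-to-event variables will be analyzed using the log-rank test" without stated stratification. The documents give no 5-year risks from which to size a gain, so stratifying by gallbladder status is optional and not a defect to correct. The primary analysis and the target of 280 are not affected.

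**What to change.** In section 20a, make these the treatment comparisons:

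- **Total procedure time and time required for stone removal:** linear regression of log time on arm, maximum stone diameter, stone number, common bile duct diameter and the two stratification factors, reported as a ratio of geometric means with 95% CI.
- **Lithotripsy and clinical success:** logistic regression on arm, maximum stone diameter and stone number, reported as a standardised risk difference with 95% CI. Keep to these two covariates given the roughly 34 lithotripsy events expected.

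Take covariate values only from imaging done before randomisation, since allocation is open and later measurements could be influenced by it. Keep the unadjusted tests as supportive. Stratifying the 5-year biliary analysis by gallbladder status may be added.

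The cost is wording and a little more analysis, with no additional patients. The covariate list and model form must be fixed in advance; because the analysts are not blinded (section 17a), this is best done now. The sponsor should confirm that stone number and duct diameter are recorded from pre-randomisation imaging. If they are not, the case report form needs those fields.

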**Primary endpoint**			
Procedure-related AE rate	Proportion of patients experiencing procedure-related AEs after protocol intervention	Incidence proportion	Within 30 days from the procedure
**Secondary endpoints**			
Type and severity of procedure-related AEs	Classified using ASGE lexicon; detailed criteria applied for bleeding and pancreatitis (see Notes)	Descriptive	Within 30 days from the procedure
Technical success rate	Completion of ESBD or EST according to protocol	Binary outcome	Day of procedure
Clinical success rate	Complete stone removal in a single session	Binary outcome	Day of procedure
Total procedure time	Time from cannulation to completion of stone removal	Continuous (minutes)	Day of procedure
Time required for stone removal	Time from end of ESBD or EST to completion of stone removal	Continuous (minutes)	Day of procedure
Proportion of cases requiring lithotripsy	Use of mechanical lithotripsy (excluding mechanical tools used without fragmentation), electrohydraulic lithotripsy, or laser lithotripsy	Incidence proportion	Day of procedure
Stone recurrence rate	Reappearance of bile duct stones post-removal	Incidence proportion	5-year follow-up
Time to stone recurrence	Days from successful stone removal to confirmed recurrence	Time-to-event	5-year follow-up
Biliary event rate	Any biliary event (e.g., stone recurrence, cholangitis, cholecystitis, liver abscess, biliary cancer)	Incidence proportion	5-year follow-up
Time to biliary event	Days from successful stone removal to occurrence of any biliary event	Time-to-event	5-year follow-up
**Notes on adverse event definitions** The definitions and severity grading of procedure-related adverse events will follow the ASGE lexicon [7]. Among these, bleeding and pancreatitis are the most anticipated adverse events in this study and represent key safety outcomes; therefore, more detailed criteria are specifically defined for these two events **-Bleeding:** *Intra-procedural bleeding*: requires hemostatic intervention (excluding preventive measures) *Post-procedural bleeding*: confirmed by endoscopy or imaging study such as computed tomography, or inferred from clinical findings such as hematemesis, melena, or a drop in hemoglobin level that cannot be explained by other causes **-Pancreatitis:** The diagnosis is established when at least two of the following three criteria are met: (1) acute abdominal pain and tenderness in the upper abdomen, (2) elevated levels of serum or urinary pancreatic enzymes, and (3) imaging findings indicative of acute pancreatitis [8]			

*AE* adverse event, *ASGE* American Society for Gastrointestinal Endoscopy, *ESBD* minimal endoscopic sphincterotomy with balloon dilation, *EST* endoscopic sphincterotomy

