### Methods in analysis to handle protocol non-adherence and any statistical methods to handle missing data {20c}

The primary analysis will follow the intention-to-treat principle, including all randomized participants in the groups to which they were assigned, regardless of protocol adherence. A per-protocol analysis may be performed as a sensitivity analysis to assess the robustness of the findings.

For missing data, an available-case analysis will be used as the primary approach. If the extent or pattern of missing data is substantial, appropriate methods such as multiple imputation may be considered in sensitivity analyses.

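### Time to biliary event starts at stone clearance, a post-randomisation outcome likely to differ by arm, so this secondary comparison omits never-cleared patients and events before clearance

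*Protocol article*

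**What the plan says.** Table 1 of the protocol article defines two long-term time-to-event endpoints with the same starting point:

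- Time to biliary event: "Days from successful stone removal to occurrence of any biliary event".
- Time to stone recurrence: "Days from successful stone removal to confirmed recurrence".

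The same table treats removal as an outcome. Clinical success is "Complete stone removal in a single session". The time-to-event rows do not say whether successful means cleared in one session or cleared eventually.

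The companion proportion, the biliary event rate, is "Any biliary event (e.g., stone recurrence, cholangitis, cholecystitis, liver abscess, biliary cancer") over 5 years, with no clearance condition.

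Under Statistical methods {20a}, time-to-event variables are compared by log-rank test and Kaplan–Meier curves, with Cox models for adjusted analyses. Section {20c} describes the primary analysis as "including all randomized participants in the groups to which they were assigned".

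The Background {6a} reports that ESBD had "significantly lower rates of requiring multiple sessions (35.1% vs. 12.8%, *P* < 0.001"), EST first, in a retrospective comparison.

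**The concern.** A randomised time-to-event comparison is protected when the clock starts at a point that treatment cannot influence. Here it starts at an outcome of treatment, and the plan's own rationale expects the arms to differ on outcomes of this kind.

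Two things follow if the definition is applied as written:

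1. A patient who is never cleared has no time zero and cannot enter the risk set.
2. A patient cleared at a later session enters late. Cholangitis, cholecystitis or liver abscess while stones remain is a biliary event by Table 1's list, but it precedes time zero and has no valid event time.

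If EST patients more often need further sessions, more of their early events go uncounted. The EST curve then looks better than it should, and a real long-term benefit of ESBD could be understated. The Discussion expects the long-term results to inform practice guidelines, so the definition matters even for a secondary endpoint.

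**Working it through.** **Plan's own figure.** The article gives no event count or power for the long-term endpoints. Its only planning figure is 280 patients, for the primary endpoint. Inputs: 15.8% vs 4.4%, two-sided alpha 0.05, power 80%, 1:1 allocation, 10% loss. The two-proportion formula with continuity correction gives 126 per arm, and 126 / 0.90 = 140 per arm, or 280 in total. The figure reproduces. It is used below only as the denominator.

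**Patients with a delayed or absent time zero.** Inputs: 140 per arm (Sample size {14}); multiple sessions 35.1% EST and 12.8% ESBD (Background {6a}).

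- EST: 140 × 0.351 = 49.1
- ESBD: 140 × 0.128 = 17.9
- Difference: 35.1 − 12.8 = 22.3 percentage points

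**How many are excluded depends on the meaning of successful.**

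- *Single-session clearance.* All of these patients lack a time zero. 140 − 49.1 = 90.9 EST and 140 − 17.9 = 122.1 ESBD patients remain. The loss is (49.1 + 17.9) / 280 = 24% of the trial, unevenly split.
- *Eventual clearance.* Only the never-cleared are excluded. The article gives no such rate. Assuming a share of the multi-session patients:

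| Share never cleared (assumed) | EST excluded | ESBD excluded |
|---|---|---|
| 10% | 4.9 | 1.8 |
| 25% | 12.3 | 4.5 |
| 50% | 24.6 | 9.0 |

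The remaining multi-session patients enter, but from a later origin.

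**Events before time zero.** Let q be the risk of a biliary event while awaiting a repeat session, taken as equal in both arms (assumed). Events missed per arm = patients awaiting × q. Between-arm difference missed = 22.3 points × q.

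| q (assumed) | EST events | ESBD events | Difference missed |
|---|---|---|---|
| 5% | 2.5 | 0.9 | 1.1 points |
| 10% | 4.9 | 1.8 | 2.2 points |
| 15% | 7.4 | 2.7 | 3.3 points |

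A patient with a further event after clearance would still be counted for that later event, so the last column is the loss if none of them has one.

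**Selection, single-session reading only.** Suppose treatment has no effect on biliary events, and every patient not cleared in one session under ESBD would also not be cleared under EST. Then 64.9% are cleared under either technique, 22.3% only under ESBD and 12.8% under neither. With 5-year risk r in the easily cleared and k × r in the others, the risk among cleared patients is r for EST and (0.649 r + 0.223 k r) / 0.872 for ESBD. The apparent hazard ratio, ESBD to EST, is ln(1 − ESBD risk) / ln(1 − EST risk).

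- r = 10%: k = 1.5, 2, 3 gives 1.14, 1.27, 1.56
- r = 15%: k = 2, 3 gives 1.28, 1.58
- r = 20%: k = 2 gives 1.30

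The true value is 1.0 throughout. Both r and k are assumptions.

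**The case against.** Much of the case on the other side stands.

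- **The events are not lost to the trial.** The biliary event rate has no clearance condition and can count them in every randomised patient. Section {22} also collects all adverse events after the intervention begins, and procedure-related ones within 30 days enter the primary endpoint. The gap is in the time-to-event version.
- **A reader might infer a breach of a stated intention-to-treat commitment.** The sentence in {20c} is worded for the primary analysis, and {11b} concerns protocol deviators. Neither clearly promises an all-randomised population for these secondary endpoints.
- **A reader might take 49 and 18 as patients removed.** The 35.1% and 12.8% count multiple sessions and do not measure failed clearance. Table 1 attaches the single-session condition to clinical success only, so eventual clearance is at least as natural a reading. Most of these patients would then only start later, and if sessions are close together the shift is small against 5 years. The rates also come from one retrospective study.
- **Recurrence presupposes removal.** Counting residual stones as failure would turn it into a composite that overlaps clinical success, so an all-randomised recurrence analysis is not required.
- **Randomisation is not an ideal origin either.** The procedure may come up to 14 days after enrolment, and only severe cholangitis is excluded at entry. A clock from randomisation could pick up pre-procedure disease.

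The remaining argument is that handling rules belong in the analysis plan, which is not shown. That would cover a missing rule. Here, however, the article fixes the time origin itself, and under that origin a pre-clearance event has no valid time.

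**Conclusion.** The point holds for time to biliary event. Its origin is a post-randomisation outcome that the plan's own rationale suggests will differ by arm. As written, the comparison omits never-cleared patients and biliary events between the index procedure and clearance.

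About 49 EST and 18 ESBD patients of 140 each would have a delayed or, if never cleared, absent time zero, provided the retrospective rates carry over to this trial. The between-arm difference missed is about 1.1 to 3.3 percentage points for an assumed 5 to 15% event risk while awaiting a repeat session. The direction is against ESBD, so the definition would not create the hypothesised benefit but could hide one. The hazard ratios of 1.14 to 1.58 apply only under the single-session reading and if hard-to-clear patients carry higher long-term risk. They show what that reading could do and are not a forecast.

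The true size cannot be fixed from the article, which defines neither successful removal nor the interval between sessions and gives no never-cleared rate. The effect is confined to secondary long-term endpoints. The primary endpoint and sample size are untouched. For time to recurrence, the from-clearance clock is defensible, and the need is for a correct label. The change is worth making but is not critical.

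**What to change.** 1. **Time to biliary event.** Measure from the date of the index procedure to the first biliary event, in all randomised patients analysed as allocated, whether or not stones have been cleared. Use the randomisation date for patients who have no procedure. State that only new events after the origin count, so that cholangitis present at entry is not scored, and state whether residual stones alone count as an event.
2. **Supportive analysis.** Keep the from-clearance version, labelled as restricted to cleared patients.
3. **Time to stone recurrence.** Keep the from-clearance clock, and state that it compares cleared patients and is not an all-randomised comparison. Report the number never cleared in each arm beside it.
4. **Definition.** Say whether successful removal means single-session or eventual clearance.

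The cost is a change to Table 1 and matching analysis-plan wording, notified as an amendment under {25}. Randomisation runs through the central system and procedural data go into the electronic case report form, so little new collection should be needed. The sponsor should confirm that dates of repeat sessions and of events between sessions are captured. Recruitment is scheduled to run to 31 March 2027, so the change can be made well before the 5-year data mature.
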